#### Statistical analysis

Data of all randomised participants excluding those with self-documented diabetes will be evaluated. The primary analysis will be performed on the study population of T1 compliers with non-missing primary outcome of knowledge. The secondary analysis set will be the subset of compliers of T1 and T2.

The persons who have prematurely terminated the study without completely documented knowledge outcome of T1 will be compared with the study population on the basis of the parameters which are assessed before randomisation (age, sex, education, life satisfaction, and pre-study knowledge about elevated blood glucose), using appropriate statistical tests (chi-square test, Fisher's exact test, t-test or Wilcoxon test). Furthermore, the subgroup of the T1/T2 compliers will be compared with the study population of T1 compliers in a similar manner.

Outcomes will be compared between intervention and control group on an 'intention to treat' basis. For the description of the population in terms of relevant basic parameters - according to distribution - frequency tables, prevalences with 95% confidence intervals or mean values with standard deviations will be calculated. Scores on knowledge and quality of the decision and satisfaction will be evaluated by average scale scores with standard deviations and percentiles. The estimates will be carried out in the intervention and control group respectively in total and stratified for relevant subgroups, e.g. age (40-49 years or older) and sex. To test any effects of the intervention, statistical comparisons will be performed - according to distribution - by chi-square or Fisher's exact test, t-test or Wilcoxon's rank sum test. The tests for each target variable is to be defined before the evaluation.

The primary outcome is an ordinal score with values 0-8. The distributions between intervention and control group will be compared primarily by Wilcoxon's rank sum test. In a secondary analysis the outcome "good knowledge" is defined by dichotomisation of the ordinal knowledge score using a predefined cut point of 5 (≥ 5 versus <5). Intervention and control group will be compared by chi-square test.

The association between this primary outcome and predictors is estimated using multiple ordinal logistic regression models. A continuation-ratio logit model will be fitted [33]. To simplify the interpretation of the results the scale of the knowledge score will be reduced to 3 ordered values by the predefined classes 0-2, 3-5 and 6-8. The predictors are first examined by univariate models. Then, multiple models considering age, sex, socio-economic variables and participation in a blood glucose test will be discussed.

Then, multiple models considering age, sex, socio-economic variables, participation in a blood glucose test and pre-study knowledge about elevated blood glucose will be discussed. A final multiple regression model will be fitted.

A secondary analysis will be performed on the subpopulation of participants at T1 and T2 considering the ordinal outcomes "attitude" and "intention to undergo uptake a metabolic testing". These variables will be described non-parametrically and control and intervention group will be compared using Wilcoxon's rank sum test.

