#### Intervention

Participants are presented either internet-based EBPI (experimental group) or standard information (control group). A widely used brochure published in the internet and two articles of popular websites are used as standard information on subthreshold elevated blood glucose levels or diabetes [10-12]. The standard information offers information about prevention, early detection, sequelae and treatment of diabetes mellitus. The EBPI summarises the existing knowledge from the scientific literature on the topic.

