#### Study execution

Participants obtain the internet information (EBPI or standard, respectively) on blood glucose disorders, metabolic testing (diabetes-testing) and prevention strategies. The survey is carried out at three points in time (T0/T1, T2), with the first two times during one visit to the website. T0 or T1 is the questioning before or after reading the information, so that the gain of knowledge and a characterisation of later drop-outs is ascertainable. T2 is the online follow-up survey two weeks after the first online session (see Figure 1).

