**Figure 1 F1:**
[figure not shown]
**Progress of intervention**.

The variables of the T0-survey and some user behaviour, e.g. point where participants quit the study, will be recorded for later drop-out-analysis.

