#### Randomisation

Randomisation takes place immediately before presentation of the information, deposited on a random number generator. To gain a balanced distribution of the study population characteristics, a stratified block randomisation is conducted (4 strata defined by women/men and 40-49 years/50 years and older, 1:1 randomisation between intervention and controls within each stratum using blocks of size 10).

Crossover between the study groups is not possible, because the IP-addresses of the participants are identified by the system.

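### The primary analysis is labelled intention to treat but is a complete-case analysis of T1 completers, open to arm-dependent loss after randomisation

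*Protocol article*

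**What the plan says.** All references are to the protocol article.

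Three sentences in Statistical analysis bear on who is analysed. The first describes the data in scope: "Data of all randomised participants excluding those with self-documented diabetes will be evaluated". The second sets the primary set: "The primary analysis will be performed on the study population of T1 compliers with non-missing primary outcome of knowledge". Two paragraphs later comes the label: "Outcomes will be compared between intervention and control group on an 'intention to treat' basis".

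The timing is given elsewhere. Under Randomisation: "Randomisation takes place immediately before presentation of the information". Under Study execution, T1 is the questionnaire completed after reading, in the same website visit as T0. Under Intervention, the experimental arm reads the EBPI, while for the control arm "A widely used brochure published in the internet and two articles of popular websites are used as standard information".

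Attrition was foreseen. Statistical analysis states: "The persons who have prematurely terminated the study without completely documented knowledge outcome of T1 will be compared with the study population". The variables are age, sex, education, life satisfaction and pre-study knowledge, all described as assessed before randomisation. The text at Figure 1 adds that the "point where participants quit the study, will be recorded for later drop-out-analysis".

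**The concern.** Intention to treat is generally read as covering everyone randomised, whatever they did afterwards. The stated primary set depends on an event after randomisation, namely reaching the end of the T1 knowledge test. Between randomisation and that event, participants read material that differs by arm, so both how many leave and who leaves may depend on the arm.

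If leaving is related to knowledge and the pattern differs by arm, the completers are no longer comparable groups. The primary test could then show a difference where there is none, or hide one that exists. The trial is designed around a small difference (0.20 SD), so a modest bias is not negligible beside it. A result reported as intention to treat would give readers no warning of this.

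**Working it through.** **1. The plan's own figure.** Sample size and statistical power gives 527 evaluable participants per group for 0.20 SD, 90% power and two-sided α = 5%, by a t-test approximation.
- Normal approximation: n = 2 × (1.960 + 1.282)² / 0.20² = 525.4, so 526.
- Noncentral t: 526.3, rounded up to 527, with power 90.04% at 527.

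The figure reproduces, so the sample size is not in error. It counts evaluable participants, however. That gives precision among completers and no protection against selection.

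**2. Order of events.** T0 questionnaire → randomisation → reading of arm-specific material → T1 knowledge test. Every loss between randomisation and T1 follows assignment. The primary rule removes all of these people from the test.

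**3. Illustrative size.** The document gives no completion rate, no difference by arm and no relation between finishing and knowledge. All three are assumed here.

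Model: knowledge and the tendency to finish are bivariate normal with correlation ρ. A fraction p of an arm finishes. With no true effect, completers in that arm lie above the arm's mean by ρ × φ(z_p)/p SD, where z_p is the p-quantile of the standard normal.

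| p | φ(z_p)/p |
|---|---|
| 0.8 | 0.350 |
| 0.7 | 0.497 |
| 0.6 | 0.644 |
| 0.5 | 0.798 |

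The bias is ρ times the difference between the arms. With 527 completers per arm the test statistic shifts by bias × √(527/2) = bias × 16.23. The false-positive rate is P(|N(shift, 1)| > 1.96). The small reduction in variance among completers is ignored.

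| Completion | ρ | Bias (SD) | Share of 0.20 SD | Shift | False-positive rate |
|---|---|---|---|---|---|
| 70% v 80% | 0.2 | 0.2 × (0.497 − 0.350) = 0.029 | 15% | 0.48 | about 8% |
| 60% v 80% | 0.3 | 0.3 × (0.644 − 0.350) = 0.088 | 44% | 1.43 | about 30% |
| 50% v 80% | 0.5 | 0.5 × (0.798 − 0.350) = 0.224 | 112% | 3.64 | about 95% |
| 80% v 80% | any, equal in both arms | 0 | 0 | 0 | 5% |

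The third row is an extreme, shown only to bound the range.

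If the same bias runs against a true 0.20 SD effect, power is P(Z < (0.20 − bias) × 16.23 − 1.96). This is about 79% in the first row and 44% in the second, against 90% planned.

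**4. A second model.** Let the odds of finishing rise by a fixed factor per SD of knowledge in both arms (1.5, 2 or 3, again assumed).
- 80% v 70% completion: bias 0.04, 0.06 or 0.08 SD; false-positive rate 10%, 18% or 32%.
- 80% v 60% completion: bias 0.08, 0.12 or 0.17 SD; false-positive rate 25%, 54% or 85%.
- Equal 80% completion, with selection in one arm only (factor 2): bias 0.13 SD.

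The last case shows that equal completion rates alone would not settle the matter.

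**The case against.** The section can be read as a hierarchy: data in scope (all randomised without diabetes), a primary subset (T1 completers) and a secondary subset (T1 and T2 completers). On that reading, intention to treat means only that people are analysed in their assigned arm. This is fair. A reader might infer three incompatible populations, but the text does not force that, and the completer rule is stated openly. What remains is a label that promises more than the set delivers.

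Attrition was also anticipated: T0 data and quit points are kept and a drop-out comparison is planned. This softens the point. As written, though, the comparison pools the arms, so it could miss opposite patterns in the two, and it has no stated consequence for the primary result. Pre-study knowledge enters only the later regression models, not the Wilcoxon test.

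Other stronger readings are not supported:
- **No missing-data analysis exists.** A condensed article may leave this to a full protocol or SAP that is not shown, so its absence is not counted here.
- **The EBPI is longer or harder and drives out weaker readers.** No section says so, and the EBPI was piloted with 41 participants. The direction of any bias is unknown.
- **The diabetes exclusion also biases the arms.** The document does not say when diabetes history is asked. The list of variables for the drop-out comparison need not be the whole T0 questionnaire, so this would be conjecture.

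**Conclusion.** The point holds as a mislabelled primary set with a real opening for selection bias. The stated primary test is a complete-case comparison of participants as randomised, and it should not be called intention to treat. That conclusion rests on the document alone.

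The size of the bias does not. Under the two milder illustrations it is 0.03 to 0.09 SD against a design difference of 0.20 SD, with a false-positive rate of about 8% to 30%. It is zero if completion and selection are the same in both arms. A reader might infer that the primary result will be biased. The document supports only that it could be, in either direction, and that the pooled drop-out comparison would neither reliably detect the bias nor correct it.

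**What to change.** 1. Rename the primary set complete-case, analysed as randomised, and remove the intention-to-treat label from it.
2. Report the numbers randomised and completing T1 in each arm, and make the planned drop-out comparison by arm.
3. Add a pre-specified supportive analysis of all randomised participants without diabetes, with T1 knowledge multiply imputed within arm from T0 knowledge, age, sex, education and life satisfaction.
4. Add a scenario that departs from missing at random. If T0 knowledge is measured on the same 0–8 scale, which the article does not state, this can be a no-gain scenario for those who left.
5. Interpret the primary result in the light of these analyses. They are supportive, and agreement need not become a second condition for success.

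The cost is a change of wording and a little more programming, since the T0 data on drop-outs are already to be recorded. The supportive estimate may be less favourable or less precise than the complete-case one.

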#### Sample size and statistical power

The main outcome is knowledge, on which the sample size calculation is based. The knowledge questionnaire includes 8 items. Each item is rated right/wrong or not completed, which will be awarded with 0 or 1 point. Result of the knowledge test therefore cover 0-8 points. The statistical power using primarily Wilcoxon's rank sum test was estimated roughly using the power calculation of the corresponding t-test assuming approximate normal distribution. Nothing was known about the distribution of the ordinal outcome. A sample size of 527 evaluable participants per group will be enough to detect a difference of 0.20 σ of the expected values between intervention and control group by 90% power using a significance level of α = 5% and a 2-sided test (σ = common standard deviation on both groups). In view of the planned multiple regression analysis and the secondary analysis of the ordinal outcome a relatively large sample size was planned.

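### The T2 drop-out check compares the T1/T2 compliers with the whole T1 group that contains them, so its independent-samples tests are conservative at every return rate and can miss real attrition

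*Protocol article*

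**What the plan says.** The Statistical analysis section of the protocol article defines two nested sets. For the primary set, "The primary analysis will be performed on the study population of T1 compliers with non-missing primary outcome of knowledge". For the second, "The secondary analysis set will be the subset of compliers of T1 and T2".

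Two drop-out comparisons follow. The first is worded so: "The persons who have prematurely terminated the study without completely documented knowledge outcome of T1 will be compared with the study population". Its variables are baseline ones (age, sex, education, life satisfaction and knowledge before the study), and it is to be carried out "using appropriate statistical tests (chi-square test, Fisher's exact test, t-test or Wilcoxon test"). In the second, "the subgroup of the T1/T2 compliers will be compared with the study population of T1 compliers in a similar manner". The closing words of that sentence carry over the variables and the tests of the first comparison.

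The T1/T2 set is then put to use: "A secondary analysis will be performed on the subpopulation of participants at T1 and T2", with attitude and intention compared between the arms.

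**The concern.** All the listed tests, when applied to two groups of people, assume that nobody is in both groups. In the T2 check everyone in the first group is also in the second. The word appropriate in the text does not resolve this, because each listed test meets the same difficulty with nested groups.

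The overlap acts twice, and both times towards a non-significant result. It dilutes the difference, because the returners sit on both sides of the comparison. It also inflates the nominal standard error, because the formula counts the shared people as two independent samples. A check meant to characterise those lost before T2 could then show no difference although the people lost did differ from those who stayed. The comparisons of attitude and intention, two of the five outcomes, rest on that set.

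**Working it through.** **Inputs from the article.** "A sample size of 527 evaluable participants per group" (Sample size and statistical power), so N = 2 × 527 = 1,054 T1 compliers. The same section gives 0.20 SD, two-sided 5% and 90% power for the comparison of arms.

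**Assumptions.** The article states neither the share q of T1 compliers who also complete T2 nor the baseline difference d (in SD) between T2 returners and non-returners. I take q from 30% to 90% and d = 0.20 and 0.30.

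**The plan's own figure.** The normal approximation gives 2 × (1.960 + 1.282)² / 0.20² = 525.4, so 526 per group. The exact t-test gives 526.3, so 527, with power 0.900. The stated 527 is reproduced.

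**The T2 check as written.**

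1. The mean of all T1 compliers is q × (returner mean) + (1 − q) × (non-returner mean). Returner mean minus whole-group mean is therefore (1 − q) × d.
2. Standard error that an independent-samples test assumes: σ × sqrt(1/(qN) + 1/N) = σ × sqrt((1+q)/(qN)).
3. True standard error of subset mean minus whole-group mean: σ × sqrt(1/(qN) − 1/N) = σ × sqrt((1−q)/(qN)).
4. Inflation factor r = sqrt((1+q)/(1−q)), which exceeds 1 for every q above zero.
5. True difference over true standard error: d × sqrt(N q (1−q)). The comparison of returners with non-returners has this same value, so the underlying information is identical. The test as written in effect requires it to exceed 1.96 × r instead of 1.96.
6. Real type I error: 2 × (1 − Φ(1.96 r)). Power is approximately Φ(d × sqrt(N q (1−q)) − 1.96 r) as written, and the same expression with r = 1 for disjoint groups.

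**Worked case, q = 0.70 and d = 0.20.** The compared difference is 0.30 × 0.20 = 0.06 SD. The assumed standard error is sqrt(1.7/737.8) = 0.0480 and the true one sqrt(0.3/737.8) = 0.0202, a ratio of 2.38. The standardised difference is 0.20 × sqrt(1054 × 0.21) = 2.975. Power as written is Φ(2.975 − 4.666) = 0.05; for disjoint groups it is Φ(2.975 − 1.960) = 0.85.

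| Return q | SE too large by | Real type I error (nominal 0.05) | Power, 0.20 SD: as written v disjoint | Power, 0.30 SD: as written v disjoint |
|---|---|---|---|---|
| 30% | 1.36 | 0.008 | 0.62 v 0.85 | 0.96 v 0.994 |
| 40% | 1.53 | 0.003 | 0.57 v 0.89 | 0.96 v 0.998 |
| 50% | 1.73 | 0.0007 | 0.44 v 0.90 | 0.93 v 0.998 |
| 60% | 2.00 | 0.00009 | 0.23 v 0.89 | 0.80 v 0.998 |
| 70% | 2.38 | 0.000003 | 0.05 v 0.85 | 0.42 v 0.994 |
| 80% | 3.00 | 4 × 10⁻⁹ | 0.0005 v 0.74 | 0.02 v 0.97 |
| 90% | 4.36 | about 10⁻¹⁷ | 0 v 0.50 | 0 v 0.83 |

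**Simulation (2,000 runs per setting).** At 70% return and 0.20 SD, the t-test rejected in 0.05 of runs as written and 0.84 with disjoint groups; the Wilcoxon test in 0.04 and 0.83. With no true difference, both tests rejected in about 5% of runs with disjoint groups and in none as written. The formulas hold for both tests.

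**The case against.** **The check is only descriptive.** The article makes this test neither a gate nor a decision rule, and setting a subset beside its parent set is a legitimate description. That stands: no effect estimate or test of the intervention changes, and the article nowhere says that a non-significant result will be taken as proof of representativeness. But the plan attaches significance tests to the comparison, and their p-values are miscalibrated.

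**The loss is not always severe.** A reader might infer that the check will almost always be non-significant. The document does not support that. It gives no return rate, and T2 is a separate session two weeks later, so low return cannot be excluded. At 30% return the check still has power 0.62 for 0.20 SD, and for 0.30 SD it has 0.80 to 0.96 at 30% to 60% return. The loss is worst when return is high, which is also when the fewest people are missing. What remains is that the check is conservative at every return rate.

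**Pooled arms.** A reader might also infer that both drop-out checks pool the arms and so cannot show selection that differs by arm. The text defines the groups by completion status and does not mention arm; it neither states pooling nor excludes a split. In a condensed article whose analysis plan is not shown, that silence is not an error.

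**The T1 drop-out check.** One might extend the criticism to the first comparison in the same paragraph. It does not apply there: people without a complete T1 knowledge outcome and the T1 study population share no members, so the listed tests are valid.

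**Conclusion.** The point holds as a fault in what the article states: independent-samples tests are planned on two groups of which one contains the other. The direction does not depend on any assumption. For every return rate the tested difference is diluted and the standard error overstated, so the real type I error lies below the nominal 5% and power below that of the disjoint comparison.

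The size does depend on assumptions, namely N = 1,054, the return rate and the amount of selection. For 0.20 SD the shortfall in power runs from moderate at 30% return to near-total at 80%. For 0.30 SD it is slight up to 50% return and large from 70%.

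The scope is narrow. It concerns the supportive drop-out check for the secondary T1/T2 analysis of attitude and intention. The primary knowledge analysis at T1 and the sample size are unaffected.

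**What to change.** Change the comparison group in the one sentence: T1 compliers who completed T2 against T1 compliers who did not, on the same pre-randomisation variables and with the same tests. The groups are then disjoint and the listed tests hold their nominal level. This costs one sentence and needs no further data or analysis. The T1 drop-out comparison can stay as it is. A breakdown of the drop-out tables by arm would be a useful optional addition, but it does not correct anything the article states.

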### Study design and setting

Pilot testing covered feasibility and acceptability testing of the instruments and procedures. The testing of the instruments took place via focus groups (15 participants) and via postal evaluation (31 participants). Procedures were tested online in several passes, primarily among employees of the participating project partners. In October 2009, the information has been made available to the study population via web-based assess. We invite visitors of the internet pages of the cooperating health insurance company, Techniker Krankenkasse (TK), and the German Diabetes Centre to take part in the study. Incentives such as books and wellness funds are drawn in order to increase the response rate. Individuals who agree to participate and give their informed consent are randomly assigned to the experimental (evidence-based consumer information) or the control group (standard information). Randomisation is stratified according to sex and age.

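### The primary Wilcoxon comparison of T1 knowledge is valid but leaves out the pre-study knowledge score already collected, so it may give up precision that costs nothing to recover

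*Protocol article*

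**What the plan says.** The Statistical analysis section of the protocol article describes the outcome, "The primary outcome is an ordinal score with values 0-8", and then fixes the test: "The distributions between intervention and control group will be compared primarily by Wilcoxon's rank sum test". It attaches no covariate or stratification to that test.

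Knowledge is also surveyed at T0, before the information is read. Under Study execution the purpose of the T0 and T1 surveys is given as "so that the gain of knowledge and a characterisation of later drop-outs is ascertainable". The Statistical analysis section confirms the timing when it lists "the parameters which are assessed before randomisation (age, sex, education, life satisfaction, and pre-study knowledge about elevated blood glucose") as the basis for comparing drop-outs with the study population.

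Pre-study knowledge is also used in the continuation-ratio logit models described after the primary test. There the score is reduced to the classes 0–2, 3–5 and 6–8. The predictors named are age, sex, socio-economic variables, previous blood glucose testing and, in a second step, pre-study knowledge. Study arm is not named.

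The sample size section states: "A sample size of 527 evaluable participants per group will be enough". The target is a standardised difference between the arms of 0.20, tested two-sided at the 5% level with 90% power. The section describes this as a rough t-test approximation to the Wilcoxon test, with nothing known about the distribution of the score.

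**The concern.** Participants answer the T1 questions in the same website visit as the T0 questions. If people who know more beforehand also tend to score higher afterwards, part of the spread in T1 scores is predictable from T0. An unadjusted test leaves that spread in the noise, whereas an adjusted one removes it and also takes account of any imbalance between arms in measured prior knowledge. The article gives no reason for leaving the T0 score out of the primary comparison.

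The analysis set adds a further reason. The primary analysis is restricted to participants with a T1 knowledge score, so losses after randomisation could leave the analysed arms unequal in prior knowledge. The article plans to compare drop-outs on T0 knowledge, but the primary test has no means of allowing for a difference if one is found. Adjustment would do so for the measured part.

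At stake are the power and precision of the main result, not its validity.

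**Working it through.** **Inputs from the article.** Difference 0.20 σ, two-sided α = 5%, power 90%, 527 evaluable participants per group (sample size section); unadjusted Wilcoxon test on a 0–8 score (Statistical analysis).

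**Input not in the article.** The T0–T1 correlation ρ, taken here as an assumed range from 0 to 0.7.

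**Step 1: reproduce the stated sample size.** Normal approximation: n = 2(1.960 + 1.282)² / 0.20² = 2 × 10.507 / 0.04 = 525.4, so 526 per group. With the noncentral t distribution, power is 89.98% at 526 and 90.04% at 527. The stated 527 reproduces.

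**Step 2: adjust for T0.** In normal-theory analysis of covariance the residual standard deviation is σ√(1 − ρ²). The required n is therefore 525.4 × (1 − ρ²), and power at 527 per group is Φ(0.20 × √(527/2) / √(1 − ρ²) − 1.960), where 0.20 × √(527/2) = 3.247.

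| Assumed ρ | √(1 − ρ²) | Fall in standard error | n per group for 90% power | Power at 527 |
|---|---|---|---|---|
| 0 | 1.000 | 0% | 526 | 90.1% |
| 0.3 | 0.954 | 4.6% | 479 | 92.5% |
| 0.5 | 0.866 | 13% | 395 | 96.3% |
| 0.7 | 0.714 | 29% | 268 | 99.5% |

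For example, at ρ = 0.5: 525.4 × 0.75 = 394.03, so 395; and 3.247 / 0.866 − 1.960 = 1.789, giving Φ = 96.3%.

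**Step 3: check on a 0–8 score with rank methods.** Normal variables were cut into nine categories, with a 0.20 SD shift before cutting and 527 per group (3,000 runs for power, 2,000 under no effect). The adjusted method was rank analysis of covariance on T0.

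| Assumed ρ (before cutting) | Plain Wilcoxon | T0-adjusted rank ANCOVA |
|---|---|---|
| 0 | 87.3% | 87.3% |
| 0.3 | 88.3% | 91.1% |
| 0.5 | 87.8% | 94.8% |
| 0.6 | 88.3% | 96.9% |

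The type I error rate was about 5% for both methods throughout (4.6% to 5.4%). The Wilcoxon figures slightly below 90% agree with its asymptotic efficiency under normality: 527 × 3/π = 503 effective participants per group, which gives 88.7%.

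**Step 4: do the planned regression models fill the gap?** They do not, for three reasons visible in the text: they follow the primary test, they reduce nine score values to three classes, and their predictor lists do not include study arm. An adjusted estimate of the arm difference on the full score is not among the analyses described.

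**The case against.** The strongest defence is that nothing stated is wrong. The Wilcoxon test is prespecified, suits an ordinal score of unknown distribution, is the test the sample size was meant to serve, and makes few assumptions. All of that stands. A reader might infer that the primary test is invalid or the trial underpowered. The article does not support either reading: type I error is controlled, and the stated power is met on the article's own basis. The shortfall of one to three percentage points for the Wilcoxon test lies within what the article itself calls a rough estimate.

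It is also true that the gain rests on an undocumented correlation. The article never says that T0 uses the same eight items, although speaking of a gain in knowledge suggests a comparable measure. Items written around the evidence-based information could sit near the floor before reading. At ρ = 0 there is no gain, and at 0.3 it is about 2.5 percentage points. Precision is therefore probably, not certainly, being given up.

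A reader might further object that the test ignores stratification, since "Randomisation is stratified according to sex and age". Little follows from that. The strata under Randomisation separate ages 40–49 from 50 and older, while eligibility is 50 to 69, so on these criteria the younger strata should be empty and only sex varies. Those passages need reconciling, but as a separate matter.

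Chance imbalance should not be overstated either. With 527 per group the standard error of a baseline difference is √(2/527) = 0.06 SD, and the p-value already allows for it.

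Finally, means, standard deviations and percentiles by arm are planned, and interval estimates may be specified in an analysis plan that is not shown. Their absence from the article is not held against it. What the defence does not supply is a reason to leave T0 knowledge out of the primary comparison.

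**Conclusion.** The point holds as a recommendation on efficiency. The primary comparison is valid but does not use a baseline measure that the trial collects in order to assess gain, and the later regression models do not make up for this. At 527 per group, adjustment would raise power from about 90% to 92.5%, 96.3% or 99.5% at assumed T0–T1 correlations of 0.3, 0.5 or 0.7, and would leave it unchanged at 0. Equivalently, 90% power would need about 479, 395 or 268 per group.

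These figures assume normal-theory analysis of covariance with a linear T0–T1 relation. The simulation with rank methods on a 0–8 score shows the same pattern at slightly lower power. No proportional-odds model was simulated, so the figures are only a guide to what that option would gain.

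**What to change.** Before any outcome data are examined, prespecify as primary a T0-adjusted comparison of the arms on the full 0–8 T1 score. Either rank analysis of covariance or a proportional-odds model would serve, with study arm, T0 knowledge, sex and age as a continuous variable. Choose one of the two in advance. Name a single primary effect measure with a 95% confidence interval, for example the covariate-adjusted mean difference in score. Keep the plain Wilcoxon test as a supportive analysis. State whether T0 uses the same eight items as T1, and how a missing T0 score is handled, so that no one in the primary analysis set is lost through adjustment.

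The cost is wording in the analysis plan; no new data or participants are needed. The downside is small but real. A model-based analysis adds an assumption (proportional odds, or linearity in the ranks), and an adjusted odds ratio, if reported, is a conditional measure that differs from the unadjusted one.
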